#### Primary endpoint

Adherence i.e. the number of the hours the patient uses the appliance every night will be measured both objectively and subjectively at 3, 6, 18 and 36 months to assess the effectiveness of the interventions in enhancing adherence to MAA.

#### Secondary endpoint

Self-efficacy, risk perception, outcome expectancy, socio-economic status and social support will be measured to assess the ability of these variables in predicting adherence.

### Trial design {8}

This study is a single-centre, superiority, two-arm, parallel-group, individually randomised clinical trial, with 1:1 allocation, designed to test the effectiveness of stage-matched intervention in enhancing patient adherence to MAA therapy in patients with OSA. In addition, we plan to recruit patients with a confirmed OSA diagnosis, specifically referred for MAA therapy from secondary care.

Ethical approval was obtained from the Greater Manchester West Research ethics committee (REC ref: 19/LO/0972 and 19/NW/0391). Patients meeting the eligibility criteria will be provided with a patient information leaflet explaining the whole study. Interested patients will be asked to sign the informed consent, after which they will be randomly assigned into two groups- intervention care (IC) and standardised care (SC). Only the investigator and chief investigator (CI) will be aware of the participant’s allocation.

Participants will be provided with a sleep diary (Additional file 1) to record their hours of sleep and MAA wear-time, which will give a subjective record of the adherence (duration of usage of MAA). The TheraMon®, a micro-sensor included in the MAA design, will be used for the objective documentation of MAA adherence. TheraMon® calculates the actual wear time by measuring temperature every 15 min and then transforms this information into wear time when the temperature ranges between two specific values. In the present study, this range is defined as 28 °C to 38 °C, which includes the vast majority of intraoral temperature values observed in an individual under normal conditions.

At baseline (T0), part of the routine clinical subject demographics to be collected will include age, gender, body mass index (BMI), and neck circumference. The AHI will also be recorded during the initial screening. Following an oral examination, upper and lower alginate impressions will be taken along with the participant's bite. In addition, participants will be asked to complete the following questionnaires at T (0):
Epworth Sleepiness Scale (ESS)Self-efficacy measure for sleep apnoea (SEMSA) modified for oral appliancePittsburgh Sleep Quality Index (PSQI)EuroQol-5 Dimension (EQ-5D)Socio-economic position questionnaireSocial support scale

The above questionnaires will provide information concerning the participant’s daytime sleepiness, personality, quality of sleep, health-related quality of life, socio-economic status and social support, respectively.

At pre-treatment T(1), participants will undergo the initial fitting of the MAA and be provided instruction on use and care.

Both IC and SC groups will be called for follow-up at 3 (T2), 6 (T3), 18 (T4) and 36 (T5) months. Any problems that the patients might be experiencing regarding MAA use will be attended to at these appointments. In addition, data indicating adherence will be collected and evaluated at the appointments both subjectively and objectively by downloading the data from the sensor using dedicated software.

Furthermore, at T(2), participants will be asked to complete the SEMSA questionnaire, whilst at T(3), participants will need to complete the ESS, SEMSA, PSQI and EQ-5D questionnaires.

One-to-one interviews will be conducted 6 months into treatment with both (*n* = 5–10) compliant and non-compliant patients. It will comprise of questions, which will address the following topics:
Patient's awareness of risks and benefits of OSABarriers and facilitators of MAA therapyThe interviews will be conducted face-to-face, recorded, and transcribed by a third-party service (Essential secretary Ltd., UK). However, due to the COVID-19 pandemic, the interviews will take place online (Microsoft® Teams or Zoom cloud meetings) to ensure the participant’s safety. Although, if the participant is comfortable travelling, the interview can be carried out in a private seminar room. Inductive content analysis will be employed to describe the experiences of OSA and MAA therapy of compliant and non-compliant patients without imposing preconceived categories and names of categories to evolve from the data [49].

## Methods: Participants, interventions and outcomes

### Study setting {9}

The study will be undertaken at the Royal London Dental Hospital, Bart’s Health NHS Trust in line with the CONSORT guidelines.

### Eligibility criteria {10}

#### Inclusion criteria

Adult (≥ 40 years old)Confirmed diagnosis of OSA (AHI ≥ 5)Referred for MAA therapyMust be able to understand, read and write English; with the assistance of a translator

#### Exclusion criteria

Insufficient teeth for MAA fabricationPoor dental or periodontal healthSymptomatic temporomandibular disorder (TMD)Previously used an MAAPatients with uncontrolled epilepsy

### Who will take informed consent? {26a}

In line with standard care, patients will be provided information regarding the study via a Participant Information sheet and what will happen to them if they agree to participate. Once the patients have agreed to participate, the research student (HT) will take written informed consent from the participants.

### Additional consent provisions for collection and use of participant data and biological specimens {26b}

Not applicable

## Interventions

### Explanation for the choice of comparators {6b}

Participants in the SC group will receive the MAA and the routine care except for the staged-matched intervention.

### Intervention description {11a}

Participants in the IC group will receive additional support in the form of behaviour change intervention. The behaviour change intervention based on the HAPA model entails delivering interventions in a staged manner. The interventions that will be provided are described in Table 1, along with the time point (Table 2).

**Table 1 Tab1:** Intervention care content specified by behaviour change techniques and linked to constructs of the HAPA model

Time Point	Intervention component	Behaviour change technique	HAPA construct targeted	Content
T(1)	Pamphlet	Information about consequences	Risk perception and outcome expectancy	The health pamphlet (Additional file 1), based on HAPA, divided into 6 sections, systematically provides information about the risk, benefits and treatment of OSA. Section 2 and 4 of the pamphlets provides spaces for the participants to discuss about risks and benefits that concern them the most. Section 3 explains the various treatments available and a brief explanation of the mechanism of the treatment.
		Action planning	Task self-efficacy	Sections 5 and 6 provide valuable information for participants on how to begin with using the appliance and to continue using it regularly. Patients are advised that is normal to struggle at time when starting a new habit and setting short-term attainable goals will aid them in their struggles to adjust. The section suggests participants to seek feedback from their family, especially their sleeping partner regarding their improvement. This type of support motivates the patient to work more towards achieving their goals.
		Goal setting		
		Problem-solving		
		Social support (unspecified)		
		Self-reward	Coping and recovery self-efficacy	In section 6, participants are told about the importance of rewarding themselves about the effort they put in to achieve their goals.
		Relapse prevention	Recovery self-efficacy	Section 6 also advises the participants to focus on the positives and think about situations that effect their capability and then about options to avoid/cope with these situations.
T(1)	Video	Credible source	Risk perception, outcome expectancy and task and coping self-efficacy	Patients will be shown a video [50] of an OSA patients who are undergoing treatment, in order for them to relate to someone who is going through the same condition as him/her. The video consists of patients talking about how OSA effected their life and its negative consequences. The patients will also talk about what motivated them to start the treatment, how has it changed their life and what does they do to use the appliance regularly. It will also consist of a specialist in the field of OSA, briefly talking about the ill effects of untreated OSA and the specific oral appliance treatment available.
		Social comparison		
		Information about the negative and positive consequences		
		Demonstration of behaviour		
		Feedback on the behaviour		
		Social support (emotional and practical)		
T(1)	Counselling	Information about health consequences	Risk perception, outcome expectancy and task self-efficacy	Participants will be given an initial counselling session in person along with their partner if they wish. During the session i.e. structured to fit the participants needs… • Their knowledge regarding OSA will be assessed • The above video will be shown • Using the information provided on the pamphlets the risks of untreated OSA and the benefits of the treatment will be discussed • If the partner is present at the appointment, they will be asked to complete a section of the pre- screening questionnaire which is part of the routine clinical examination. In the questionnaire, the partner will also be asked to indicate their and the participant’s quality of sleep. In addition, the partner will also be asked to indicate the severity of the participant’s snoring and whether it has an influence on their sleep.
		Social Support (unspecified and emotional)		
		Verbal persuasion about capability		
T(2), T(3), T(4) and T(5)	Follow up at sleep clinic	Monitoring the behaviour and the outcome	Coping and recovery self-efficacy	Participants would be required to visit the sleep clinic for follow up at months 3 and 6. Their MAA usage will be assessed both objectively and subjectively by downloading the data from the micro-sensor chip embedded in the appliance and by recording the hours from their daily sleep log respectively.
		Focus on past success and verbal persuasion about capability	Coping and recovery self-efficacy	Feedback would be provided depending on the participant’s usage. Their planning sheets would be discussed, and appropriate feedback will be provided whilst encouraging them to set more active goals and plans.
		Social comparison	Coping and recovery self-efficacy	To increase their emotional support other patient’s feedbacks and successful treatment would be shared.
		Problem-solving	Coping and recovery self-efficacy	Additionally, participants will be prompted to identify common factors that act as barriers for them in using the appliance and will be helped to find solutions to overcome such factors tailored to the participants needs.
3, 6, 18, and 21 weeks	Booster phone calls	Verbal persuasion about capability	Coping and recovery self-efficacy	Participants will receive calls at weeks 3, 6, 18 and 21 approximately 10–15 min in duration, prompting them to keep working towards their goals and stating that they are capable of achieving them.
		Social support unspecified	Coping and recovery self-efficacy	Participant’s partner’s experience of the treatment will also be discussed by asking them to share their thoughts on the participant’s improvement.
		Problem-solving	Coping and recovery self-efficacy	Additionally, participants will be prompted to identify common factors that act as barriers for them in using the appliance and will be helped to find solutions to overcome such factors tailored to the participants needs.

**Table 2 Tab2:** Intervention care and standardised care components

Time point	Intervention care group	Standardised care group
*T0 (Baseline)*	• Questionnaires - ESS, SEMSA (Modified for Oral Appliance) PSQI, EQ-5D, Socio-Economic Position and Social Support	• Questionnaires - ESS, SEMSA, PSQI, EQ-5D, Socio-economic position, Social Support scale
*T1 (Pre-treatment)*	• Providing instruction about how to use the MAA • Health pamphlet based on HAPA theory • Assessment of knowledge of OSA and involvement of the partner in education • A brief education focusing on the benefits associated with MAA • 10-min video education about OSA, emphasising the negative consequences if OSA is untreated • Risk perception communication • Setting Goals and action planning (steps to facilitate the use of MAA)	• Providing instruction about how to use the MAA • Health pamphlet about OSA and MAA
*T2 (3 months into treatment)*	• Phone calls to be made at 3 and 6 weeks - Problem-solving - Evaluation of the patient and partner perception of treatment - Verbal encouragement - Setting attainable goals and action planning • Follow up at Sleep Clinic -Assessment of MAA use -Problem Solving -Verbal Encouragement -Sharing other Patient’s Feedbacks and successful treatment experiences • Questionnaire -SEMSA	• Follow up at Sleep Clinic - Problem-solving - Assessment of MAA use • Questionnaires -SEMSA
*T3 (6 months into treatment)*	• Phone calls to be made at 18 and 21 weeks - Problem-solving - Partner involvement in treatment and family support - Verbal encouragement - Setting attainable goals and action planning • Follow up at sleep clinic - Assessment of MAA use - Problem-solving - Verbal encouragement - Sharing other patient’sfeedbacks and successful treatment experiences • Questionnaires - ESS, SEMSA, PSQI, EQ-5D • One-to-one interviews	• Follow up at Sleep Clinic - Problem-solving - Assessment of MAA use • Questionnaires - ESS, SEMSA, PSQI, EQ-5D • One-to-one Interviews
*T4 (18 months into treatment)*	• Assessment of MAA use	• Assessment of MAA use
*T5 (36 months into treatment)*	• Assessment of MAA use	• Assessment of MAA use

### Criteria for discontinuing or modifying allocated interventions {11b}

As we are comparing the benefits of supportive information on participant’s use of a standard treatment undertaken by NHS, we do not see any specific criteria for discontinuing or modifying allocated interventions.

### Strategies to improve adherence to interventions {11c}

The study specifically aims to enhance MAA therapy adherence in patients with OSA. The strategies employed to improve adherence to the intervention i.e. the MAA therapy have been designed on the principles on the behaviour change model, HAPA. These strategies are described in detailed in Table 1.

### Relevant concomitant care permitted or prohibited during the trial {11d}

No relevant concomitant care is prohibited during the trial.

### Provisions for post-trial care {30}

Mandibular advancement therapy will continue for all patients post the trial.

### Outcomes {12}

#### Primary outcome

Adherence i.e. the number of hours the patient uses their appliance every night will be measured both objectively and subjectively at 3, 6, 18 and 36 months to assess the effectiveness of the interventions in enhancing adherence to MAA.

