### Sample size {14}

A minimum sample size of 56 patients distributed in two groups is proposed for given α (0.01) and power (0.9), for 2 randomly assigned groups, intervention care (*n* = 28), standard care group (*n* = 28). Finally, assuming a maximum of 15% dropout, a total number of 64 patients is required.

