#### Assessing the aims of the study

In order to assess the aims of the study, we will test each of the repeated measures first by themselves using a repeated measures ANOVA controlling for groups:
Adherence – reported, times 3, 6, 18, 36 difference 3–6, 6–18, 18–36Adherence – objective, times 3, 6, 18, 36 difference 3–6, 6–18, 18–36ESS, time 6, difference 0–6PSQI, time 6, difference 0–6EQ5D, time 6, difference 0–6Risk perception, times 3, 6, difference 0–3, 0–6, 3–6Outcome expectancy, times 3, 6, difference 0–3, 0–6, 3–6Self-efficacy, times 3, 6, difference 0–3, difference 0–6, 3–6

Once we understand the trends in the data, we can construct multiple regressions for Adherence variables. These can be the final measures from time 6 or the differences between them and previous times, 0 or 3. In these models, we will use the Psychosocial variables and socio-economic as predictors, beyond the group classification.

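### Sensor hours and diary hours are jointly primary at four visits, and no measure, visit or contrast is named to decide the null hypothesis

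*Protocol article*

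**What the plan says.** The Primary outcome section under Outcomes {12} defines adherence as nightly hours of use, which "will be measured both objectively and subjectively at 3, 6, 18 and 36 months to assess the effectiveness of the interventions". The Primary endpoint section gives the same two measures and four visits. Neither ranks them. The Null hypothesis section is a single statement about adherence in general.

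Under Assessing the aims of the study, the plan is that "we will test each of the repeated measures first by themselves using a repeated measures ANOVA controlling for groups". The diary entry reads "Adherence – reported, times 3, 6, 18, 36 difference", followed by 3–6, 6–18 and 18–36, and the sensor entry has the same seven items. Regressions for adherence come once the trends are understood, and of their outcomes the text says: "These can be the final measures from time 6 or the differences between them and previous times, 0 or 3". Table 3 schedules no adherence measurement at time 0.

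The Sample size section gives 28 per arm at alpha 0.01 and power 0.9. It names no measure, visit or contrast.

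On knowledge of allocation, Trial design {8} states: "Only the investigator and chief investigator (CI) will be aware". Tables 1 and 2 give intervention participants an individual counselling session, a video, usage feedback and calls at weeks 3, 6, 18 and 21, none of which is listed for standardised care. Table 1 takes subjective usage "by recording the hours from their daily sleep log respectively". The blinding section describes only the statistician as blinded.

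**The concern.** A trial with one null hypothesis needs one result that decides it, or a rule for combining several. Here the sensor could show no difference while the diary does, or the arms could differ at 3 months and not at 36. The protocol would not say in either case whether the intervention worked. The choice could then be made after the results are seen.

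The diary's equal status makes this worse. It is self-report by people who can tell which kind of care they are getting, so reporting may differ between arms even if wear does not. The protocol's own Background criticises an earlier study of type D personality and appliance adherence for relying on subjective rather than objective assessment.

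**Working it through.** **1. What the planning figures are for.** The 56 cannot be recomputed, because the article gives no effect size or SD. Working backwards with the normal approximation, n per arm = 2(z₁₋α/₂ + z₀.₉)²/d², so d = √(2/28) × (2.576 + 1.282) = 1.03 SD two-sided. (Sidedness is not stated; one-sided it is 0.96.) The design therefore fits one test of about 1 SD at alpha 0.01. The section does not say which test.

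**2. Counting the candidates.** The outcome definition gives 2 measures × 4 visits = 8. The analysis list gives 2 × (4 visits + 3 differences) = 14. Read as one overall group test per measure, the ANOVAs give 2. No reading gives 1.

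**3. Chance of at least one false positive.** Under independence it is 1 − (1 − α)^k. The correlations are assumed, as the document gives none. The simulated column uses 28 per arm, 20,000 replicates per setting, and correlations of 0.3 to 0.9 between visits and between measures.

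| What counts | k | 0.01, independent | 0.01, simulated | 0.05 (assumed), independent | 0.05 (assumed), simulated |
|---|---|---|---|---|---|
| One group effect per measure | 2 | 2.0% | 1.5–2.1% | 9.75% | 6.7–9.6% |
| Any visit, either measure | 8 | 7.7% | 3.4–7.3% | 33.7% | 13.6–30.9% |
| Any listed visit or difference | 14 | 13.1% | not run | 51.2% | not run |

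A second simulation gave all eight tests one common correlation. At 0.01 it produced 7.7%, 6.2%, 4.7% and 3.9% for correlations of 0, 0.5, 0.7 and 0.8. At 0.05 the results were 34%, 25%, 19% and 16%. These are the 4 to 8% and 16 to 34% ranges quoted; only correlations near 0.9 go lower.

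The planning alpha is not presented as a multiplicity adjustment. An even split of 0.05 over eight tests would be 0.05/8 = 0.00625, which is stricter than 0.01.

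**4. Price of keeping everything primary.** At d = 1.03 and an overall two-sided alpha of 0.01:

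| Primary tests | Alpha each | Power at 28 per arm | n per arm for 90% |
|---|---|---|---|
| 1 | 0.01 | 90% | 28 |
| 2 | 0.005 | 85.3% | 32 |
| 8 | 0.00125 | 73.6% | 39 |

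One named test keeps both planning figures. Eight with an even split would need 78 patients before dropout instead of 56.

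**The case against.** The strongest reply is that the analysis section plans one repeated measures ANOVA per measure. With two overall group tests at 0.01 the error is about 2%, which is small. That reading is available and limits the size of the problem. It does not remove it: two tests are still not one, nothing says whether the group effect, the interaction or a particular visit decides, and there is no rule if sensor and diary disagree.

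A second reply is that a statistical analysis plan may settle this. The choice of primary measure and time belongs in the protocol, however, and here the protocol does not merely omit it: it gives both measures at all four visits equal standing.

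Several stronger readings are tempting but not supported:

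- **That the false-positive risk is a quarter to a third.** This needs 0.05 per test. The only alpha in the document is 0.01.
- **That 35 quantities are tested for the main claim.** The list does contain 35, but 21 of them are ESS, PSQI, EQ-5D and the three SEMSA constructs, which are not the primary outcome.
- **That one arm is coached to report more hours.** The tables describe encouragement and feedback on using the appliance, and standardised care also has its use assessed. Differential reporting is a fair risk, but it is an inference.
- **That between-visit changes say nothing about treatment.** The intervention starts at T1, so an effect complete by 3 months and then constant would not appear in them. But the week 18 and 21 calls fall between months 3 and 6, and later changes bear on maintenance.

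**Conclusion.** The point stands in this form: no measure, visit or contrast is named as decisive, and the sample size is tied to none. At the stated alpha the chance of at least one false positive is about 4 to 8% if any of eight comparisons counts, and about 2% if only two overall group tests count. The first range assumes a common correlation between 0 and 0.8. The 16 to 34% range applies only if 0.05 per test were used. A reader might infer that the protocol declares success on any of eight comparisons. It states no success rule at all, and that is the defect.

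The more serious consequence is that a positive claim could rest on the diary alone. This assumes only that participants notice the extra care they receive. The sentence in Trial design {8} on who knows the allocation is hard to square with that and should be reconciled with Tables 1 and 2. The matter should be settled before any comparison between arms, because at present the trial's success criterion is undefined.

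**What to change.** Name objective (TheraMon) mean hours per night as the sole primary measure, with one pre-named contrast between intervention and standardised care, tested once at alpha 0.01. State that the sample size refers to that contrast.

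The 6-month value is a reasonable choice: the booster calls end at week 21, and Table 2 lists only assessment of use after 6 months. It is not the only choice. Table 1 labels the follow-up support T2 to T5, although its content mentions only months 3 and 6, and this should be reconciled with Table 2. A single sensor contrast over all visits would equally resolve the defect.

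Make the diary and the remaining visits secondary. Report between-visit differences as supportive evidence on change and maintenance. Fix the regression outcome in advance and drop the option of a difference from time 0, for which no adherence is scheduled.

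No new data or patients are needed. The cost is a protocol amendment and registry update while recruitment is under way (it began in December 2019), with notice to the sponsor, the ethics committee and participants as the protocol requires. The diary and the other visits become supportive rather than decisive.
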